### 3 Version history

The first unblinded analysis of the TARGIT Trial took place in 2010 using a reference date of 02/05/2010, on the recommendation of the DMC. The emphasis was on efficacy and early safety. The results have been published (Lancet 2010; 376: 91-102).

The second unblinded analysis took place in 2012 using a reference date of 01/06/2012, on the recommendation of the DMC in 2010 (two years after the first analysis). The emphasis was on efficacy, and mortality. The results have been published (Lancet 2014; 383: 603–13).

This SAP is for a third unblinded analysis due to take place in 2019 using a reference date of 02/05/2018 on the recommendation of the TSC (completeness of follow-up at least 95% at 5 years and 90% at 10 years). The emphasis will be on all primary and secondary endpoints and subgroup analyses.

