## 8.2 Methodology

The two arms of the trial will be compared on the basis of 'intention to treat': The methods below have been used in the previous analysis

1. Non-inferiority will be tested using the difference in binomial proportions of local recurrence in the first 5 years and its 90% confidence interval using standard methods.
2. We shall also test for any difference in survival function using the log-rank test and Wilcoxon tests, and Kaplan-Meier curves and proportional hazard regression models will be used to account for time-to event and censoring of the data; however, these shall not be used for testing non-inferiority.
3. We shall also use the integrated difference of the two survival functions to quantify the difference between the Kaplan-Meier curves for local recurrence and local recurrence free survival
4. In order to reduce the assumption of normal distribution in the above models, we shall also use the recently described method of restricted mean survival time approach for analysis of all outcomes

For the primary end point of survival without local recurrence, given the difficulties in understanding the concept of non-inferiority and the criticism that the 2.5% margin may be considered arbitrary, we will describe the main results in terms of the absolute number of events as well as 5-year Kaplan-Meier estimate (and its 95% CI) of local recurrence and local recurrence free survival for each of the randomised arms of the trial.

For the analysis of overall survival, breast cancer survival and non-cancer survival, we shall report the absolute number of events, 5-year KM estimate as well as the analyses to test the null hypothesis of equality.

Statistical significance will be defined as per the current alpha spend. If p values are used, then, for local recurrence statistical significance will be at  $p < 0.001$  (using the Lan-DeMets spending function method) (it was 0.01 at the last analysis), and for survival it will be  $p < 0.025$  (it was 0.05 at the last analysis).

We shall also consider performing these analyses using the Bayesian methods using meaningful priors from previous analyses.

We shall transparently display the results of all analysis.

The baseline comparisons between the two groups will be done using chi-squared test for categorical variables and independent two sample t-test for all continuous variables.

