### 9.4 Statistical Analysis

The major endpoint is the incidence of local recurrence. This will be compared on the basis of 'intention to treat' (i.e. all randomised patients will be analysed) and the logrank test will be used. This will be performed once the baseline data have been compared to test the randomisation and to define whether any stratified analyses are required. In addition ratios of radiological lesion size to clinical and pathological size, and of specimen weight will be compared to ensure that the extent of the surgical procedure was similar in both groups. The baseline comparisons between the two groups will be done using chi-squared test for categorical variables and independent two sample t-test for all continuous variables. Statistical significance will be defined at the  $p < 0.05$  level. We will use Kaplan-Meier curves and proportional hazard regression models to account for time-to event and censoring of the data.

In addition, exploratory subgroup analyses will be performed on the main endpoint including variables such as tumour size, grade and axillary nodal involvement. These will be stipulated in the Statistical Analysis Plan agreed by the International Steering Committee before any analysis is undertaken.

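### SAP 8.2 presents the survival threshold of p < 0.025 as an alpha spend, but survival was already tested at 0.05 in 2012, so the two looks together do not hold 5%

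*Combined protocol and SAP*

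**What the plan says.** SAP 8.2 (Methodology) introduces its thresholds with "Statistical significance will be defined as per the current alpha spend". If p values are used, local recurrence is judged at p < 0.001, with the note "using the Lan-DeMets spending function method) (it was 0.01 at the last analysis". Survival is judged at p < 0.025, with the note "it was 0.05 at the last analysis". The spending method is named beside the local recurrence level only.

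The same section commits to testing: "For the analysis of overall survival, breast cancer survival and non-cancer survival", it promises event counts, 5-year Kaplan-Meier estimates and "the analyses to test the null hypothesis of equality".

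SAP 3 (Version history) records the looks. Of the 2012 unblinded analysis it says "The emphasis was on efficacy, and mortality". Of the present one it says "This SAP is for a third unblinded analysis due to take place in 2019".

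Protocol 9.4 gives the only general level in the documents: "Statistical significance will be defined at the" 0.05 level. Protocol 10.1 sets no formal stopping boundary, and none for survival appears anywhere.

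**The concern.** A spending function divides a fixed total of type I error among successive looks. Calling a threshold an alpha spend therefore tells the reader that the error accumulated over all looks stays within that total. For survival the SAP names no total. On the usual reading of 5%, a look at 0.05 in 2012 leaves nothing to allot to a later look, yet a further 0.025 is allotted.

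What is at stake is how a survival result would be described. A difference with p < 0.025 at this look could be reported as significant under an error-controlled scheme, although the procedure over the two looks does not have that property. Mortality was already a focus of the published 2012 analysis, so a false survival claim could have arisen at either look.

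**Working it through.** **Inputs from the documents**
- Survival level at the 2012 look: 0.05 (SAP 8.2), two-sided critical value 1.960.
- Survival level at the present look: 0.025 (SAP 8.2), two-sided critical value 2.241.
- Hypothesis: equality of the arms (SAP 8.2), so the tests are taken as two-sided.
- General significance level: 0.05 (protocol 9.4).

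**Assumptions**
- The total for survival is 5%.
- The same survival comparison is tested at both looks.
- *t* = deaths at the 2012 look / deaths now. The documents give no death counts, so a range is shown.

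**Step 1. Can 0.025 be reproduced as a further spend?** The alpha spent up to a look is at least the chance of rejecting at that look. After 2012 it is therefore at least 0.05, and 0.05 − 0.05 = 0 remains. The figure 0.025 is 0.05/2, an equal split over two looks, but that split would have needed 0.025 in 2012 as well. The stated level is not reproduced under a 5% total.

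**Step 2. Direction.** Under the null hypothesis,

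P(claim at either look) = 0.05 + P(no rejection in 2012 and rejection now).

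The second term is positive whenever *t* < 1. The total then exceeds 5%, whatever the value of *t*.

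**Step 3. Size.** P = 1 − P(|Z₁| ≤ 1.960 and |Z₂| ≤ 2.241), with (Z₁, Z₂) bivariate normal and correlation √*t*.

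| *t* (assumed) | Two-look error | Excess over 5%, points |
|---|---|---|
| 0.2 | 7.03% | 2.03 |
| 0.3 | 6.84% | 1.84 |
| 0.5 | 6.43% | 1.43 |
| 0.7 | 5.93% | 0.93 |
| 0.8 | 5.63% | 0.63 |
| 0.9 | 5.29% | 0.29 |

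Bounds: if the looks were independent, 1 − 0.95 × 0.975 = 7.4%; the sum 0.05 + 0.025 = 7.5% cannot be exceeded. A simulation with 4 million draws gave 6.85%, 6.43% and 5.92% at *t* = 0.3, 0.5 and 0.7. One-sided tests at the same levels give 6.7% to 5.8% for *t* = 0.3 to 0.7.

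**Step 4. What would have held 5%.** With 0.025 now, the 2012 level could have been at most about 0.030 (*t* = 0.3), 0.034 (*t* = 0.5), 0.039 (*t* = 0.7) or 0.047 (*t* = 0.9). With 0.025 at both looks, the error would be 4.6%, 4.3% and 3.9% at *t* = 0.3, 0.5 and 0.7.

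**Contrast.** The local recurrence levels do not raise this problem: 0.01 followed by 0.001 sums to 0.011. The point is confined to survival.

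**The case against.** The strongest reply is that the 5% total is not stated. Protocol 9.4 gives its level directly after the baseline comparisons, in a paragraph about local recurrence, and mentions neither survival nor repeated looks. The plan for the 2012 analysis, which might settle the matter, is not among the documents. This stands: the 5% is an inference. It is also true that a lower nominal level at a later look is not in itself incompatible with spending. A total equal to the two-look error in the table would make the two thresholds a valid scheme. But the SAP states no such total and reserves no survival alpha for a third look, and few readers would suppose a total above 5%.

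Three further replies have some force.
- The threshold is conditional on p values being used, and SAP 8.1 puts absolute numbers first. Yet SAP 8.2 commits to tests of equality for survival, and this is the only rule given for judging them.
- The earlier 0.05 is openly disclosed. Disclosure does not make the later level a spend.
- Read alone, this look is held at 2.5%, which is stricter than the protocol's general level. That is correct, but an alpha spend is a statement about error across looks.

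A reader might also infer that 2010 was a third survival test and count it too. The documents do not support this: SAP 3 gives the 2010 emphasis as efficacy and early safety, and no survival test or level is reported for that look.

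**Conclusion.** The alpha-spend description is unsupported for survival. If the survival total is 5%, the 2012 look used all of it. That the two-look error exceeds 5% needs no assumed information ratio, only that deaths have accrued since 2012. The size does need one: about 5.3% to 7.0% for ratios 0.9 to 0.2, with a ceiling of 7.5%. The excess is modest, roughly 0.3 to 2 percentage points for a single endpoint in a single comparison.

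It would be tempting to quote one figure for the error, such as 6 to 7%. Without death counts at the two looks the documents do not support any single figure. The three survival endpoints and the two separately reported strata are a different multiplicity question and are not included here.

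This deserves correction before results are reported, but it is a matter of how a secondary endpoint is described. It does not affect the primary comparison.

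**What to change.** In SAP 8.2, confine the reference to the current alpha spend to local recurrence, and replace the survival clause by one of the following.

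- *Option 1:* Survival was tested at 0.05 in 2012. Survival p values at this third analysis are nominal and will be reported with 95% confidence intervals, without a claim of error-controlled significance.
- *Option 2:* For survival, 0.025 is a nominal level for this analysis alone. Because survival was tested at 0.05 in 2012, the cumulative two-sided error over the two analyses exceeds 5%; its value, calculated from the numbers of deaths at the two analyses, will be given in the report.

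Under option 2 the statement belongs in both the SAP and the report, and the formula in step 3 gives the value once the two death counts are entered.

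The cost is SAP and report wording, plus one short calculation under option 2. Data, design and patient care are unaffected. The downside is that a survival p value below 0.025 can no longer be presented as significant under an alpha-spending scheme. Alpha already used in 2012 cannot be recovered by any choice of level now.

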#### **10.1 Data Monitoring Committee (DMC)**

An independent DMC has been appointed and their remit agreed. They will regularly review the data collected during the trial and report to the ISC as to whether the trial should continue and make recommendations as to changes in the protocol.

Meetings will probably be scheduled annually for the first two years of the trial whilst accrual gains momentum. More frequent meetings may then be held.

There are no formal stopping rules for the trial – these may be determined in discussion with the DMC but should a difference between the treatments in local recurrence reach  $p < 0.001$  serious consideration as to whether the trial should continue will be given.

## SECTION 11

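### The p < 0.001 level for local recurrence in SAP 8.2 cannot be reproduced from the documents and does not match standard Lan-DeMets spending of 0.05, which leaves the difference tests much weaker than they need to be

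*Combined protocol and SAP*

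**What the plan says.** SAP section 3 lists unblinded analyses in 2010 and 2012 and then states: "This SAP is for a third unblinded analysis due to take place in 2019". The reference date is 2 May 2018. SAP 8.2 ties the decision level to an existing allocation: "Statistical significance will be defined as per the current alpha spend". The threshold it then sets for local recurrence is 0.001, on condition that p values are reported at all. Its stated basis, and the level used before, are given in one parenthesis after another: "using the Lan-DeMets spending function method) (it was 0.01 at the last analysis".

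Three other places bear on this:

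- Protocol 9.4 is the only place that states a general level for the trial, which is 0.05.
- Protocol 10.1 says there are no formal stopping rules. It does name one consequence of a local-recurrence difference at the 0.001 level: "serious consideration as to whether the trial should continue will be given".
- SAP 8.2, item 1, keeps non-inferiority separate: "Non-inferiority will be tested using the difference in binomial proportions of local recurrence in the first 5 years and its 90% confidence interval". Item 2 plans log-rank, Wilcoxon and proportional-hazards analyses of difference and bars them from the non-inferiority role.

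**The concern.** A spending function fixes the cumulative alpha used by each look. When the last look spends whatever remains of 0.05, the usual functions leave a final nominal level well above 0.001. Here the level falls tenfold from the second look to the third, and the SAP gives nothing from which a reader could derive that fall. The same number appears in protocol 10.1 for another purpose, prompting the DMC to ask whether the trial should go on.

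A very strict level is not conservative in a non-inferiority trial. The log-rank and Wilcoxon tests are where an excess of local recurrence with IORT would be declared. Setting them at 0.001 makes that declaration hard to reach, while non-inferiority is still judged with a 90% interval. One data set could then fail non-inferiority and also be labelled not significantly different.

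**Working it through.** **Inputs.** Levels 0.001 (third look) and 0.01 (second look): SAP 8.2. Looks in 2010, 2012 and 2019: SAP 3. Overall level 0.05: protocol 9.4. Design of 6% at 5 years, 2.5-point margin, 1116 per arm, 80% power: protocol 9.1. Randomised 3451: SAP 10. *Assumed:* p values are two-sided; information fractions; the 2010 level; 1:1 allocation (about 1725 per arm); 575 per arm as an illustrative stratum; control rates of 1% to 6%.

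**1. The plan's own design figure.** n = (1.645 + 0.842)² × 2 × 0.06 × 0.94 / 0.025² = 1115.8, so 1116 per arm. This reproduces with one-sided 0.05.

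**2. What 0.01 then 0.001 spends.** Under the null the look statistics are jointly normal with correlation √(tᵢ/tⱼ). With nothing spent in 2010, the two levels together spend 0.0109 (t₂/t₃ = 0.2), 0.0105 (0.5), 0.0101 (0.8) or 0.0100 (0.95). That is about a fifth of 0.05.

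**3. The level left at the third look.** I solved for the nominal two-sided level that brings the total to 0.05 after 0.01 at look 2. With no 2010 spend, t₂/t₃ ran from 0.2 to 0.95. Otherwise I used these eight patterns (t₁, t₂, t₃): (0.1, 0.3, 1), (0.1, 0.6, 1), (0.2, 0.5, 1), (0.2, 0.8, 1), (0.3, 0.5, 1), (0.3, 0.7, 1), (0.4, 0.9, 1), (0.5, 0.8, 1).

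| Level used in 2010 | Level left at look 3 |
|---|---|
| none | 0.042 to 0.050 |
| 0.001 | 0.042 to 0.049 |
| 0.01 | 0.035 to 0.044 |
| 0.02 | 0.025 to 0.037 |

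To leave exactly 0.001, the 2010 level must be about 0.044 (0.041 to 0.047 over the eight patterns).

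**4. Standard functions.** Choose the information time t at which each function has spent 0.01 of 0.05, treat that as the earlier look, and solve for the next one.

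| Function | t with 0.01 spent | Level at full information | Level at 80% information |
|---|---|---|---|
| O'Brien-Fleming type, 2 − 2Φ(1.96/√t) | 0.579 | 0.046 | 0.025 |
| Pocock type, 0.05 ln(1 + (e − 1)t) | 0.129 | 0.041 | 0.035 |
| Linear, 0.05t | 0.20 | 0.042 | 0.032 |

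With three looks and seven assumed information patterns, the third-look levels were 0.019 to 0.048, 0.018 to 0.026 and 0.023 to 0.032 respectively. Even the heavily front-loaded function 0.05t^0.1 gave 0.004 to 0.006.

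**5. Power for 8.5% v 6%, 1116 per arm.** SE = √[(0.06 × 0.94 + 0.085 × 0.915)/1116] = 0.01096, so z = 0.025/0.01096 = 2.280.
- At 0.001: Φ(2.280 − 3.291) = 16%.
- At 0.025: Φ(2.280 − 2.241) = 52%.
- At 0.045: Φ(2.280 − 2.005) = 61%.

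**6. Smallest observed excess reaching p < 0.001.** Solve d/√[2p̄(1 − p̄)/n] = 3.291 with p̄ = control rate + d/2. Results are in percentage points; bold marks those above the margin.

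| Per arm | 1% | 2% | 3% | 5% | 6% |
|---|---|---|---|---|---|
| 1725 | 1.5 | 1.9 | 2.2 | **2.7** | **3.0** |
| 1116 | 1.9 | 2.5 (2.46) | **2.9** | **3.5** | **3.7** |
| 575 (assumed) | **3.0** | **3.7** | **4.3** | **5.1** | **5.5** |

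In the bold cells, an observed excess between 2.5 points and the tabled value misses p < 0.001.

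**7. The two tests on one result.** Take 9.5% v 6% with 1116 per arm. The difference test gives z = 0.035/√(2 × 0.0775 × 0.9225/1116) = 3.09, p = 0.0020, so not significant at 0.001. The unpooled SE is 0.0113, giving a 90% interval of 1.6 to 5.4 points. This excludes zero and runs past 2.5, so non-inferiority is not shown.

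**The case against.** Several points on the other side are sound.

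- A reader might infer that 0.001 is impossible under Lan-DeMets. It is not: the method accepts any non-decreasing spending function, and SAP 8.2 refers to an existing allocation that it does not set out. A total near 0.0105 or a 2010 level near 0.044 would produce it.
- Protocol 9.4 does not describe 0.05 as a group-sequential total. It is simply the only overall level stated.
- A reader might infer that 0.001 was carried over from protocol 10.1. The match is exact, but it does not prove origin.
- A reader might infer that an inferior result could pass as acceptable. The documents do not support that. Any observed excess above 2.5 points puts the upper 90% limit above the margin, so non-inferiority fails whatever the p value. SAP 8.2 also leads with event numbers and 5-year Kaplan-Meier estimates, applies the level only if p values are used, and promises to display all results. Nowhere does it say that p > 0.001 will be reported as no difference.
- The clash with the margin depends on arm size and control rate. At about 1725 per arm and control rates up to 3% it does not arise. Protocol 9.2 reports recurrence of 0.3% at two years, so 6% may be far from what is seen. The 575 per arm is not in the documents.
- The power and excess figures use a two-proportion comparison at 5 years, which only approximates a log-rank test.

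These points narrow the consequence. They do not supply a derivation of 0.001. The difference tests are planned, and SAP 6 presents every result by stratum, so arms smaller than those of the whole trial are the relevant ones.

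**Conclusion.** The concern holds as an unsupported decision level. Taking 0.05 as the total, 0.01 followed by 0.001 uses only about 0.010 to 0.011 unless 2010 spent heavily. The level left at the third look is about 0.025 to 0.050 for a 2010 level between 0 and 0.02, which is 25 to 50 times the stated one. None of the standard functions tried gives the stated pair.

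The cost is power in the difference tests: 16% against 61% at 0.045, or 52% at 0.025, for the protocol's own 8.5% v 6% with 1116 per arm. A result that misses p < 0.001 with an excess above 2.5 points is possible at control rates of 3% or more with 1116 per arm, 5% or more with about 1725, and 1% or more with an assumed 575.

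It would be tempting to put 0.042 to 0.050 straight into the SAP. That range assumes the 2010 look spent nothing, which the documents do not say. All the levels rest on assumed information fractions and two-sided p values.

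**What to change.** In SAP 8.2, name the spending function and state a total two-sided alpha of 0.05. Give information fractions based on local-recurrence events at the 2010, 2012 and 2018 looks, together with the levels actually used in 2010 and 2012. Recompute the third-look level from these and replace 0.001 with the result. If an allocation exists that really leaves 0.001, document it instead. Do not fix a replacement value before the 2010 level and the event counts are in the calculation.

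Keep 0.001 only in protocol 10.1, as the DMC's prompt. Add one sentence saying that a p value above the level is not evidence of no difference.

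The cost is a few sentences and one group-sequential calculation. The downside is a somewhat higher chance of declaring a false difference than at 0.001, held at 5% overall once the 2010 spend is included.

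### SAP 8.2 gives significance levels with no stated alpha total or spending scheme: against 0.05, survival overspends, and the 0.001 for local recurrence cannot be derived and costs power to detect an excess

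*Combined protocol and SAP*

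**What the plan says.** SAP 8.2 (Methodology) states: "Statistical significance will be defined as per the current alpha spend". If p values are used, local recurrence is to be judged at p<0.001, "using the Lan-DeMets spending function method". The SAP adds that "it was 0.01 at the last analysis), and for survival it will be" p<0.025, and notes of the survival level that "it was 0.05 at the last analysis". Lan-DeMets is named for local recurrence only.

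SAP 3 (Version history) records unblinded analyses in 2010 and 2012 and says: "This SAP is for a third unblinded analysis due to take place in 2019". The levels used in 2010 are not given.

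Three other places bear on the point:
- Protocol 9.4: "Statistical significance will be defined at the" p<0.05 level. This is the only overall level in the documents, and it is not described as a spending total.
- Protocol 10.1: there are no formal stopping rules, but "should a difference between the treatments in local recurrence reach" p<0.001, continuation would be seriously considered.
- SAP 8.2, item 1: non-inferiority is tested on the difference in proportions with local recurrence "in the first 5 years and its 90% confidence interval using standard methods". Item 2 keeps the log-rank, Wilcoxon and regression analyses out of the non-inferiority test.

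**The concern.** A spending function releases alpha cumulatively up to a fixed total. The level at each look follows from the total, the function and the information accrued. A reader given two successive levels should be able to check them, and here cannot.

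What can be checked does not fit 0.05. Testing survival at 0.05 in 2012 would use the whole of that total and leave nothing for a later test. For local recurrence, a level that drops from 0.01 to 0.001 as information grows is unusual, and it leaves most of the total unspent.

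The two departures have different consequences. For survival, the false-positive rate exceeds 5%. For local recurrence, the departure is conservative about declaring a difference. In a non-inferiority trial that is not automatically safe, because a real excess on the experimental arm becomes harder to call significant.

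**Working it through.** **Inputs.** Levels: SAP 8.2. Overall level 0.05: protocol 9.4, taken as the total (assumption). Margin of 2.5 points and 6% five-year baseline: protocol 9.1. Randomised: 3,451 (SAP 10), so 3,451/2 ≈ 1,725 per arm if allocation was 1:1 (assumption). Two-sided tests are assumed, because SAP 8.2 does not state sidedness. Information fractions are not given, so a range is shown.

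**Design figure.** n per arm = (1.645 + 0.842)² × 2 × 0.06 × 0.94 / 0.025² = 1,116. This reproduces protocol 9.1 at one-sided 0.05.

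**Survival.** Let t be the 2012 information as a fraction of that at this analysis. Z₁ (2012) and Z₂ (now) are bivariate normal with correlation √t. Cumulative error = P(|Z₁|>1.960 or |Z₂|>2.241).

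| t | 0.3 | 0.5 | 0.7 | 0.9 |
|---|---|---|---|---|
| Error | 0.068 | 0.064 | 0.059 | 0.053 |

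The result exceeds 0.05 for every t below 1. A nominal 0.025 does not add 0.025: at t = 0.5 it adds about 0.014 (0.064 − 0.050). One-sided tests give 0.052 to 0.067 over the same range.

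**Local recurrence, alpha used.** P(|Z₁|>2.576 or |Z₂|>3.291) is 0.0108 at t = 0.3, 0.0105 at t = 0.5 and 0.0100 at t = 0.9. About 0.039 of a 0.05 total is unspent over these two looks.

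**Local recurrence, level left.** Suppose only 0.01 was spent before and this look is final. Solving P(|Z₁|>2.576 or |Z₂|>c) = 0.05 gives a nominal level of 0.043 at t = 0.3, 0.045 at t = 0.5 and 0.050 at t = 0.9. If 2010 was tested at 0.01, the level left is about 0.038 to 0.042. If it was tested at 0.03, it is about 0.018 to 0.024 (looks at fractions 0.2/0.5/1 to 0.4/0.7/1).

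**Local recurrence, standard functions.** O'Brien-Fleming-type, Pocock-type, power (1, 2, 3) and Hwang-Shih-DeCani (−4, +4) functions were run at total 0.05 with five sets of fractions, two of them with this look not final. None gave 0.01 then 0.001. At looks 0.3/0.6/1, O'Brien-Fleming-type gives 0.0004/0.011/0.046 and Pocock-type 0.021/0.020/0.023. The smallest third-look level in any run was 0.0064. The pair 0.01 and 0.001 totals 0.05 only if 2010 was tested at about 0.044 to 0.046.

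**Power to declare a 2.5-point excess.** Power = Φ(0.025/SE − z), with SE² = [p₀(1−p₀) + p₁(1−p₁)]/n, p₁ = p₀ + 0.025, and z = 1.960 or 3.291. For p₀ = 6% and n = 1,725, SE = 0.00882 and 0.025/SE = 2.835. This gives Φ(0.875) = 81% and Φ(−0.456) = 32%.

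| Baseline p₀ | 1,725 per arm: p<0.05 | p<0.001 | 862 per arm: p<0.05 | p<0.001 |
|---|---|---|---|---|
| 6% | 81% | 32% | 52% | 10% |
| 3% | 95% | 64% | 73% | 24% |
| 1% | 99.9% | 95% | 94% | 59% |

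The 862 columns illustrate a stratum holding half the trial; actual stratum sizes are not given. They matter because SAP 6 presents all results by stratum. At a 6% control rate with 1,725 per arm, the observed excess must reach about 2.95 points for p<0.001 (1.68 for p<0.05), which is above the margin itself. These figures use five-year proportions, whereas the planned difference tests use all follow-up, so they indicate scale only.

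**The case against.** The strongest reply is that p-values are not the main output. SAP 8.2 makes them conditional, and promises event counts and five-year Kaplan-Meier estimates with 95% intervals by arm for local recurrence, with all analyses displayed. The non-inferiority interval is untouched by the 0.001. If the true excess equals the margin, that interval passes only about 5% of the time at a single look. This stands, and it limits the harm to the difference p-values. A reader might infer that the plan conceals excess recurrence; the documents do not support that.

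A reader might also see the 90% interval and the 0.001 as two incompatible rules for one endpoint. They are not. SAP 8.2 separates the non-inferiority test from the difference tests, and these address different hypotheses. What remains open is whether the interval allows for repeated looks. If the same one-sided 0.05 rule applied at all three analyses, the cumulative error would be about 9.8% to 11.0% (looks at 0.4/0.7/1 to 0.2/0.5/1).

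Three more cautions stand. The 0.05 total is inferred from protocol 9.4. Lan-DeMets is not assigned to survival, so survival cannot be said to break it. Lan-DeMets admits any increasing function and the 2010 level is missing, so misfit for local recurrence is not strictly proved.

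The reply does not dispose of the point. SAP 8.2 invokes an alpha spend for both endpoints and commits to testing equality for survival. Nobody can verify the levels as written.

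**Conclusion.** The point holds as follows. Taking 0.05 as the total, survival at 0.05 then 0.025 carries a cumulative two-sided error of 5.3% to 6.8%, whatever the spending function. The excess is modest but certain for any fraction below 1. Local recurrence at 0.01 then 0.001 uses 1.0% to 1.1% over two looks and matches no standard function tried.

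The cost in power depends on the event rate. For the whole trial it is severe at the design's 6% baseline (81% to 32%) and small at 1% (99.9% to 95%). It is larger within strata. Protocol 9.2 reports only 0.3% recurrence at two years, so the lower baselines cannot be dismissed.

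Two further inferences are not supported. The 0.001 equals the monitoring prompt in protocol 10.1, but no document says it was taken from there. Nor is 0.045 the correct replacement: that value assumes t = 0.5, nothing spent in 2010 and no later look. That the two departures both happen to suit the experimental arm is interpretation, not something the documents show.

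**What to change.** Before the third unblinded analysis, amend SAP 8.2 to:

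1. State, for local recurrence and for survival, the total alpha, sidedness, spending function, information fractions from event counts, and the levels used in 2010, 2012 and now. Reconcile these with p<0.05 in protocol 9.4.
2. Replace 0.001 for local recurrence with the level derived from that scheme.
3. For survival, report estimates with 95% confidence intervals, and either make no significance claim or disclose the cumulative error.
4. State whether the 90% non-inferiority interval is adjusted for repeated looks.

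The cost is one short calculation and one paragraph. The downside is that a survival claim at p<0.025 is lost or must be qualified.
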